## 8.2 Discontinuation criteria for each patient and its handling

The necessary items are recorded up to the traceable time point in the case report form and the “discontinuation report form” in the following patients.

- 1) When a patient has died.
- 2) When a patient cannot be contacted and becomes untraceable.

However, if the transfer destination is known, the patient will be tracked by obtaining data from the transfer destination facility or by calling, and tracing will be continued.

- 3) When a patient requests discontinuation from research participation (patient information prior to discontinuation can be used).
- 4) When a patient has requested consent withdrawal (patient information after registration cannot be used).

- 5) When the lead principal physician or study physician deemed that research participation should be discontinued.

Patients in whom any of the following are applicable are not considered discontinued, with normal observation period inspections continued to the extent possible, and information up to the time point of 96 weeks collected.

- 1) Patients who transitioned to renal replacement therapy (dialysis, kidney transplantation).
- 2) When a patient has requested discontinuation of darbepoetin alfa use.
- 3) When the lead principal physician or study physician deemed that darbepoetin alfa use should be discontinued due to adverse events, etc.

The lead principal physician or study physician will make efforts to provide the best possible treatment to the patient even after discontinuation of research participation.

If it was determined after registration that a patient did not meet the eligibility criteria at the time of registration, then this will be considered “ineligible after registration,” and research participation will be concluded for the patient. Adverse event information up to 30 days after the decision to complete participation will be reported for patients in whom darbepoetin alfa was administered even once.

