### 10.1.3 Observation period (from start of treatment-96 weeks later)

Report the information closest to each survey point among the inspection results included in the permissible range.

Start of treatment: day of blood tests; urine tests can be performed up to -4 weeks, blood test HbA1c up to -8 weeks)

Weeks 2, 4, 6, 8, 10, 12, and 16 after the start of treatment:  $\pm 1$  week

Weeks 24, 36, 48, 60, 72, 84, 96 after the start of treatment:  $\pm 6$  weeks

|        |                                             |                                             |                                                                                                                                                                                     |                                                                                                                                     |
|--------|---------------------------------------------|---------------------------------------------|-------------------------------------------------------------------------------------------------------------------------------------------------------------------------------------|-------------------------------------------------------------------------------------------------------------------------------------|
| 1
* | Darbepoetin alfa administration status      | Administration date                         | yyyy/mm/dd                                                                                                                                                                          |                                                                                                                                     |
|        |                                             | Administration route                        | Intravenous administration, subcutaneous administration, other (details)                                                                                                            |                                                                                                                                     |

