#### 10.1.5 When discontinuing / withdrawing consent for participation in research

Provide answers within four weeks of discontinuation or consent withdrawal from research participation. Items from two onwards are not needed for patients who withdraw consent. Investigations during the normal observation period are continued if the patient can be traced even after the discontinuation of darbepoetin alfa administration or after event occurrence.

|    |                                                             |                                           |                                                                                                                                            |                                                                                                                                                                                                                                                                                                                                                                                                                                |
|----|-------------------------------------------------------------|-------------------------------------------|--------------------------------------------------------------------------------------------------------------------------------------------|--------------------------------------------------------------------------------------------------------------------------------------------------------------------------------------------------------------------------------------------------------------------------------------------------------------------------------------------------------------------------------------------------------------------------------|
| 1  | Research participation discontinuation / consent withdrawal | Discontinuation / consent withdrawal date | yyyy/mm/dd                                                                                                                                 |                                                                                                                                                                                                                                                                                                                                                                                                                                |

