## 12. Definition of endpoints

### 12.1 Primary endpoints

#### 12.1.1 Renal function deterioration

Composite events of each event occurring 12 weeks after the start of treatment (see “10.4.1 Event – Renal function deterioration”) are set as renal function deterioration. The number of days until occurrence is calculated, with 12 weeks after the start of treatment as the starting point.

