#### 12.1.2 CVD event

Composite events of each event occurring 12 weeks after the start of treatment are set as the CVD event. The number of days until occurrence is calculated, with 12 weeks after the start of treatment as the starting point.

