### 12.3 ERI

The following five indices are considered new candidates for the ESA response indices (ERIs) to be investigated.

- ERI-1A (index according to one time point at 12 weeks)

$$\frac{\text{DA administered dose 12 weeks after the start of treatment (}\mu\text{g)}}{\text{Hb concentration 12 weeks after the start of treatment (g/dL)} \times \text{weight 12 weeks after the start of treatment (kg)}}$$

- ERI-1B (index according to one time point at 12 weeks)

$$\frac{\text{DA administered dose 12 weeks after the start of treatment (}\mu\text{g)}}{\text{Hb concentration 12 weeks after the start of treatment (g/dL)}}$$

- ERI-2A (index that considers the cumulative administered dose up to 12 weeks and changes in Hb concentration)

$$\frac{\text{Total DA administered dose up to 12 weeks after the start of treatment } (\mu\text{g})}{\text{Amount of change} \times \text{weight at 12 weeks (kg)}}$$

- ERI-2B (index that considers the cumulative administered dose up to 12 weeks and changes in Hb concentration)

$$\frac{\text{Total DA administered dose up to 12 weeks after the start of treatment } (\mu\text{g})}{\text{Amount of change}}$$

- Change in Hb concentration (changes in Hb concentration up to 12 weeks)

$$\text{Hb concentration at 12 weeks (g/dL)} - \text{prior Hb concentration (g/dL)}$$

A similar index is created for the ERI index from the Hb concentration and darbepoetin alfa administered at 16 weeks and at 24 weeks in addition to that at 12 weeks, and the associations between these indices and event occurrence are also investigated. When the ERI index at 12 weeks favorably predicts event occurrence, then whether the ERI index composed of the values at week 10, 8, 6, 4, and 2 favorably predicted the event occurrence is confirmed in order.

New indices are further explored if no associations between these index candidates and renal function deterioration or CVD events were found.

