### 13.3.1 Renal function deterioration, CVD event investigation

A proportional hazards model that includes the following covariates is applied, and the factors that affect event occurrence are investigated. Covariates are added or decreased as required for the investigation of the model. Hb concentration values at each measurement time point up to 24 weeks instead of week 12 of administration are also investigated. The presence of diabetic complications, arteriosclerosis, and chronic inflammation should also be considered as stratification factors. These analyses are used to investigate the prediction equation for event occurrence from the covariates.

- Age; sex; weight; eGFR, serum albumin, hemoglobin concentration, high-sensitive CRP, NT-pro BNP, folic acid, vitamin B12, serum iron, serum ferritin, and TSAT 12 weeks after the start of treatment; the presence of diabetic complications, arteriosclerosis, chronic inflammation, malignant tumor complications, hemorrhagic lesion complications, collagen disease and rheumatic disease complications, concomitant immunosuppressant or steroid use, and other myelosuppressive factors; and the darbepoetin alfa administered dose (total administered dose, administered dose 12 weeks after the start of treatment).

Next, the cut-off values of each ERI are gradually increased from the minimum value to the maximum

value; a time-dependent ROC curve of the survival time data with censoring is created, and the AUC is compared. If the cut-off value is set from the ROC curves of each obtained ERI, then these are divided into two groups at the cut-off value, Kaplan-Meier plots are created, and the annual event occurrence rate (human-year method) and 95% confidence intervals are estimated. The cut-off values of the ERIs may also be investigated using the cross-validation method, if considered useful.

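### The supplementary week-16 and week-24 response indices and Hb values are related to events counted from week 12, so some events precede the predictor and can alter it

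*Protocol*

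**What the plan says.** Section 12.1.1 fixes the time origin of the renal endpoint: "The number of days until occurrence is calculated, with 12 weeks after the start of treatment as the starting point". Section 12.1.2 uses the same origin for cardiovascular events: "Composite events of each event occurring 12 weeks after the start of treatment are set as the CVD event".

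The five candidate indices in section 12.3 are built at week 12, which matches that origin. The section then adds later versions: "A similar index is created for the ERI index from the Hb concentration and darbepoetin alfa administered at 16 weeks and at 24 weeks", and "the associations between these indices and event occurrence are also investigated". For the proportional hazards model, section 13.3.1 adds: "Hb concentration values at each measurement time point up to 24 weeks instead of week 12 of administration are also investigated".

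The measurement windows are in section 10.1.3. They are ±1 week for week 16 and ±6 weeks for the group "Weeks 24, 36, 48, 60, 72, 84, 96 after the start of treatment", so a week-24 value may date from anywhere between weeks 18 and 30. The value closest to the survey point is to be reported.

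Follow-up does not end with a non-fatal event. Section 8.2 lists among those not treated as discontinued "Patients who transitioned to renal replacement therapy (dialysis, kidney transplantation"), together with patients who stop darbepoetin alfa (DA). Section 10.1.5 adds: "Investigations during the normal observation period are continued if the patient can be traced even after the discontinuation of darbepoetin alfa administration or after event".

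The efficacy set in section 13.2.2 looks at eligibility, DA use around week 12, and Hb at the start and at week 12. It sets no condition at week 16 or week 24.

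**The concern.** A predictor should be known before the outcome that it is meant to predict. With time zero at week 12 and the index measured at week 16 or 24, every event in between counts as an outcome of an index not yet measured when the event occurred. Two problems follow.

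- **Reverse influence.** A cardiovascular admission or the start of dialysis may change Hb, the DA dose or both. The later index can then carry the trace of the event and be associated with it without predicting anything.
- **Selection.** A patient who dies between week 12 and the measurement has no value. Everyone who has a value is certain to have survived from week 12 to the measurement date.

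At stake is how the week-16 and week-24 results are read. A hazard ratio, ROC curve or cut-off obtained this way would not describe how the index performs when used prospectively at week 16 or 24.

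**Working it through.** **The plan's own figure.** Section 13.1 expects 480–568 events in two years from 2,000 patients at 13.1 per 100 person-years. The expected count is 2,000 × 2 × 0.131 = 524, and 524 ± 1.96 × √524 = 524 ± 44.9, which is 479 to 569. The stated range reproduces as a Poisson interval, so the rate is used below.

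**Events before the later measurements.** Assume 2,000 at risk at week 12, a constant hazard of 0.131 per year applied to one endpoint, and no loss to follow-up. Events from week 12 to week w are 2,000 × (1 − exp(−0.131 × (w − 12)/52.18)).

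| Up to week | Events since week 12 | Share of weeks 12–96 |
|---|---|---|
| 16 | 20 | 5% |
| 24 | 59 | 16% |
| 30 (far edge of the week-24 window) | 88 | 23% |
| 96 | 380 | 100% |

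Assumed rates from 5 to 20 per 100 person-years give 23 to 90 events before week 24. The share stays at 15–16%.

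**Effect on the estimate.** The protocol does not say how many early events alter the index, or by how much, so both are assumptions here. The simulation took N = 2,000, the same hazard, and a standard normal index with no true effect. The index was shifted upward for a chosen fraction of the patients whose event fell in weeks 12–24. A Cox model was then fitted with time zero at week 12. Ranges cover separate sets of 150 to 1,000 runs.

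| Early events that shift the index | Shift (SD) | HR per SD | p < 0.05 |
|---|---|---|---|
| 25% | 0.5 | 1.02 | 5–8% |
| 25% | 1.0 | 1.04 | 10–11% |
| 50% | 0.5 | 1.04 | 11–12% |
| 50% | 1.0 | 1.08 | 30–34% |
| 100% | 0.25 | 1.04 | 11–12% |
| 100% | 0.5 | 1.08–1.09 | 31–36% |
| 100% | 1.0 | 1.16–1.17 | 81–85% |

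If half of the early-event patients are shifted and the other half have no index, the HR is 1.04 (0.5 SD) or 1.10 (1.0 SD), with 13% or 40% of runs significant.

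Starting the clock at week 24 among patients still event-free gives an HR of 1.00 and 4–7% significant in 1,000 runs, whichever shift is assumed.

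The direction is also open. If DA is stopped after an event, the dose-based index falls and the bias changes sign.

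**The case against.** The strongest reply is that this touches only a supplementary part of the plan. The main indices are measured at week 12 and paired with a week-12 origin, and the week 2–10 indices precede it. Section 13.3 says that no hypotheses are verified and that P-values are exploratory, and it leaves further detail to the statistical analysis plan. All of this stands, and it limits the severity. It does not remove the point: the protocol itself fixes week 12 as the origin in its endpoint definitions and pairs it with later predictors, so an analysis plan that used a landmark would depart from those definitions.

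Four stronger readings are tempting, and the protocol does not support them.

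- **The later indices would wrongly beat the week-12 index in a comparison that the study sets out to make.** No section sets up such a contest. The only ordered sequence in 12.3 runs backwards from week 12, and 13.3.1 compares AUCs across the indices without naming later weeks.
- **A false-positive rate above 80% is to be expected.** That needs every early event to shift the index by a full SD. Patients who die early have no index to shift, and the protocol does not say that crossing an eGFR threshold changes Hb or dose.
- **About 88 events precede the week-24 index.** This is an upper bound with every value taken at week 30, whereas 10.1.3 asks for the value closest to the survey point.
- **Renal rates are materially distorted by patients already dialysed or transplanted before week 12.** Section 13.2.2 does not remove such patients if they remain on DA, but their number cannot be derived and is probably small. Exclusion 5.2(1) bars dialysis or transplant planned within 24 weeks of registration, and 13.2.2 removes those who stopped DA within 12 weeks.

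Exclusion 5.2(1) also bears on the count of 59. Treatment starts within eight weeks of registration, so the exclusion reaches treatment week 16 at least and week 24 at most. Early renal events may therefore be fewer than a constant hazard implies, although unplanned starts remain possible.

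**Conclusion.** The point holds for the week-16 and week-24 indices and Hb values, and only for those. Followed as written, the protocol relates them to about 20 and 59 events that happened before the measurement. Those counts assume a constant 13.1 per 100 person-years, 2,000 patients at risk at week 12 and no loss to follow-up.

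The bias in the hazard ratio cannot be fixed from the protocol. Under the assumptions examined it runs from negligible (about 1.02 per SD) to appreciable (about 1.16 per SD), and its sign could reverse. This is a should-fix matter: a real misalignment in an exploratory extension, with a simple remedy, that leaves the main analysis intact.

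**What to change.** Add a short paragraph to sections 12.1, 12.3 and 13.3.1:

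- For each week-16 or week-24 index or Hb value, time starts at the actual measurement date. Only patients free of that endpoint and under observation on that date are included, and only later events count.
- The same origin applies to the Cox models, the time-dependent ROC curves, and the Kaplan-Meier plots and annual rates.
- If indices from different weeks are compared, use the same patients and the latest landmark for all of them.
- As a minor addition, leave patients already on maintenance dialysis or transplanted at the landmark out of the renal risk set. This applies to the week-12 landmark too.

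No new data are needed. The week-24 analysis gives up about 59 of some 380 events, leaving about 321; the week-16 analysis gives up about 20, leaving about 360. The week-24 loss is somewhat larger if many values fall late in the window.

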### 8.1 Recommended renal anemia treatment

This research is an observational study, so the following treatment methods are recommended.

Among CKD patients diagnosed with renal anemia, those for whom ESA administration was deemed necessary will receive the expected DA according to the package insert and observed for 96 weeks from the start of treatment (see Section 8.1.1 for target values of renal anemia treatment).

The participants in this study will include patients who did not receive ESA within 12 weeks prior to registration, and inspections in this research will be implemented following consent acquisition. DA administration will begin within eight weeks after registration.

The final administration of DA during the observation period will be performed immediately before 96 weeks after the start of treatment, but treatment will be continued as necessary after the completion of the observation period.

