#### 【Dosage and administration】

- Initial dose

Adult: A usual adult dose of 30 µg of darbepoetin alfa (genetic recombination) per session is administered subcutaneously or intravenously once every two weeks.

- Maintenance dose

Adult: When improved effects are seen for anemia, a usual adult dose of 30–120 µg of darbepoetin alfa (genetic recombination) per session is administered subcutaneously or intravenously once every two weeks. When anemia improvement is maintained with an administration once every two weeks, then the starting dose is twice the dose at that time; dosing frequency is changed to once every four weeks, and 60–180 µg per session can be administered subcutaneously or intravenously once every four weeks.

The dose may be adjusted according to the extent of anemic symptoms, age, etc., but the maximum administered dose is set at 180 µg per session.

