#### 【Dose adjustment】

The dose should be adjusted with reference to Table 8.2-1 in cases where dose adjustments are necessary, such as when appropriate increases in the Hb concentration or hematocrit value are not observed in the initial administration period, or when the Hb concentration or hematocrit

value deviated from the target range for two consecutive weeks during the maintenance administration period. When increasing doses, do so one step at a time as a general rule.

The table below shows the dose adjustment table for subcutaneous administration. The latest package insert for intravenous injections was followed.

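### The ERI look-back to weeks 4 and 2 has no Hb-only reference, so an early ERI-1 result cannot be told apart from Hb level or body weight while doses are still near the common start

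*Protocol*

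**What the plan says.** Section 12.3 of the protocol names five candidate indices. With all quantities taken at week 12, ERI-1B is dose divided by Hb, and ERI-1A is dose divided by Hb × weight. ERI-2A and ERI-2B divide cumulative dose by the Hb change (with weight in ERI-2A). The fifth index is the Hb change itself. If the week-12 index predicts well, the plan checks in order "whether the ERI index composed of the values at week 10, 8, 6, 4, and 2 favorably predicted the event occurrence". No index is left out of that look-back.

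The dosing excerpt in Section 8.1.2 starts with "A usual adult dose of 30 µg of darbepoetin alfa (genetic recombination) per session", given once every two weeks. On increases it says "When increasing doses, do so one step at a time as a general rule". The scheme leaves room to deviate: "This research is an observational study, so the following treatment methods are recommended" (Section 8.1); "The dose may be adjusted according to the extent of anemic symptoms, age, etc"; and an adjustment is allowed "such as when appropriate increases in the Hb concentration or hematocrit value are not observed in the initial administration period", with no earliest week given.

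In Section 13.3.1 the cut-off of each ERI is moved from its minimum to its maximum, "a time-dependent ROC curve of the survival time data with censoring is created, and the AUC is compared". A cut-off taken from those curves may then split patients into two groups for Kaplan-Meier plots and event rates. The same section fits proportional hazards models with Hb, weight and dose as separate covariates, and also examines Hb at other visits up to week 24.

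**The concern.** ERI-1 is meant to measure response by relating the dose a patient needs to the Hb that patient reaches. It can do so only when doses differ between patients. At weeks 2 and 4, under the recommended scheme, many doses may still be the common starting dose. The numerator then carries no information, and what remains is the Hb level, or Hb × weight. Hb level that early is largely the level the patient had before treatment.

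Low Hb or low weight may predict renal or CVD events for reasons unrelated to the drug. The look-back could then end by reporting that a response index works as early as week 2. A cut-off would look like a response threshold but be an Hb threshold: at 30 µg, ERI-1B = 3.0 is the same statement as Hb = 10.0 g/dL (30/10.0 = 3.0). This bears on the study's aim of finding a response index and its cut-off. The effect is probably strongest in the ACS of Section 13.2.3, which is defined by compliance with the recommended scheme.

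**Working it through.** The plan gives no figure to reproduce here. The check has an exact part and a simulated part.

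**Exact part.** An ROC curve made by moving a cut-off across an index depends only on the order in which the index ranks patients. Let every patient have the same dose c = 30 µg.

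- ERI-1B = c/Hb falls strictly as Hb rises, so its AUC equals that of Hb (low Hb counted as high risk).
- ERI-1A = c/(Hb × weight) falls strictly as Hb × weight rises, so its AUC equals that of Hb × weight. It does not equal that of Hb.
- ERI-2A, ERI-2B and change in Hb still use the Hb change.

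**Simulated part.** The document does not say what share of patients is still on 30 µg at weeks 2 or 4. It was taken as 70% to 100%, the rest moved to 60 µg (the next step in Table 8.2-1) and weighted towards poor responders. Further assumptions, none from the document:

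- 200,000 patients and a simple binary-event AUC;
- baseline Hb 9.8 g/dL (SD 0.9), capped below 11;
- early Hb rise 0.4 g/dL (SD 0.5 or 0.8);
- weight 58 kg (SD 11);
- risk driven either by response only or by Hb level, with or without a weight effect.

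Four of the settings:

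| Risk driven by | On 60 µg | Hb | ERI-1B | Hb × weight | ERI-1A | Change in Hb |
|---|---|---|---|---|---|---|
| Response, weight effect, SD 0.5 | 0% | 0.566 | 0.566 | 0.582 | 0.582 | 0.623 |
| | 10% | 0.566 | 0.578 | 0.582 | 0.595 | 0.623 |
| | 30% | 0.566 | 0.587 | 0.582 | 0.601 | 0.623 |
| Hb level, weight effect, SD 0.5 | 0% | 0.602 | 0.602 | 0.600 | 0.600 | 0.550 |
| | 10% | 0.602 | 0.594 | 0.600 | 0.594 | 0.550 |
| | 30% | 0.602 | 0.579 | 0.600 | 0.581 | 0.550 |
| Response, no weight effect, SD 0.8 | 0% | 0.639 | 0.639 | 0.572 | 0.572 | 0.699 |
| | 10% | 0.639 | 0.645 | 0.572 | 0.597 | 0.699 |
| | 30% | 0.639 | 0.653 | 0.572 | 0.623 | 0.699 |
| Hb level, no weight effect, SD 0.8 | 0% | 0.622 | 0.622 | 0.564 | 0.564 | 0.581 |
| | 10% | 0.622 | 0.614 | 0.564 | 0.568 | 0.581 |
| | 30% | 0.622 | 0.602 | 0.564 | 0.570 | 0.581 |

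Five results follow.

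1. With all patients on 30 µg the equalities are exact. The rank correlation of ERI-1B with 1/Hb is 1.000; that of ERI-1A with 1/Hb is only about 0.44 to 0.50.
2. With 5%, 10%, 20% and 30% on 60 µg, the rank correlation of ERI-1B with 1/Hb falls to about 0.96-0.98, 0.92-0.94, 0.84-0.88 and 0.77-0.83. Its AUC still stays close to that of Hb: the largest gap in the table is 0.602 − 0.579 = 0.023.
3. ERI-1A can leave its reference further behind when risk follows response: 0.623 − 0.572 = 0.051 at 30% on 60 µg. There the dose increases themselves carry response information.
4. Hb after a common dose still contains response: its correlation with simulated response was about 0.51 to 0.69, so response accounts for about 0.51² = 0.26 to 0.69² = 0.48 of its variance.
5. When risk follows Hb level and all doses are equal, ERI-1B beats change in Hb (0.602 against 0.550; 0.622 against 0.581). An AUC comparison among the ERIs alone would then prefer it.

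**The case against.** The strongest defence has four parts.

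- **Dosing is not fixed.** The scheme is only recommended, may be individualised, and sets no earliest week for a change. The plan defines a separate compliance set, so it expects deviations. This stands: a reader might infer that nearly all patients are on 30 µg at weeks 2 and 4, but the document does not say so. The point has to be conditional on that share.
- **Early Hb is not free of response.** A reader might infer that early ERI-1 says nothing about ESA response. That goes too far, because Hb after a common dose is baseline plus response. A reader might also infer that the AUC of both ERI-1 indices is simply that of Hb. That holds for ERI-1B only.
- **The plan already looks at Hb.** The Cox models examine Hb at several visits, with weight and dose as separate covariates, and change in Hb is itself a candidate index. This stands in part. A careful analyst could notice the problem from those results. But the AUC comparison and the cut-off are where an index is chosen, and that step contains only the ERIs.
- **The step is late, conditional and exploratory.** Week 2 is reached only after success at week 12 and in order, in a study with no hypothesis to confirm, and reference curves could sit in the SAP, which is not at hand. This limits the weight of the point. It does not remove it, since the protocol itself fixes the index formulas, the look-back weeks and the ROC comparison.

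**Conclusion.** The point holds as an inexpensive improvement to an exploratory step. It is not an error that invalidates the study's main analysis.

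To the extent that patients are still on the common starting dose at weeks 4 and 2, ERI-1B is Hb in another form and ERI-1A is Hb × weight in another form. That part is exact. With up to 30% of patients on the next dose step, the AUC of ERI-1B remains within about 0.02 of that of Hb; this rests on the simulation assumptions above. No such narrow bound applies to ERI-1A. Response is confounded with baseline Hb at those weeks rather than missing. As the ROC step is written, an early ERI-1 success could not be separated from an effect of anaemia level or body weight.

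**What to change.** In Sections 12.3 and 13.3.1:

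- add Hb alone and Hb × weight at the same visit as reference predictors in the time-dependent ROC comparison at each look-back week;
- report the distribution of darbepoetin alfa doses at that week;
- claim early prediction by ERI-1 as a response index only if its AUC exceeds the matching reference (Hb for ERI-1B, Hb × weight for ERI-1A), and read the difference with its uncertainty;
- keep change in Hb, ERI-2A and ERI-2B in the look-back for comparison.

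The simulation suggests the comparison is informative. Once some doses differed, both ERI-1 indices rose above their references in the tabulated settings where risk followed response. Where risk followed Hb level, ERI-1B fell below its reference and ERI-1A exceeded its own by at most 0.006 (0.570 − 0.564).

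The cost is a few lines of text and two more ROC curves per visit, from Hb, weight and dose data already collected. The downside is that fewer early time points may be claimable for ERI-1.
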